## 2. Materials and Methods

The study protocol received ethics approval from the Monash University Ethics Committee (Project Number: 30472) and is registered with the Australian New Zealand Clinical Trial Registry (ACTRN12621001762842).

### 2.1. Study Setting

The intervention will run in Victoria, Australia, where the Better Health Program has not been delivered via e-Health modalities for the treatment of childhood overweight or obesity. All data collection and study/program activities will be undertaken via e-Health and with families living in Victoria. 

The obesity rate in Victoria is comparable to the obesity rate of developed countries with the highest rates of obesity, with 2 in 3 adults and 1 in 4 primary-school-aged children living with overweight or obesity [1,11]. 

### 2.2. Study Design

This study is an RCT with a qualitative component and a waitlisted control group (Figure 1). This study is pragmatic in nature because it has been developed to evaluate the web-based program as it would typically be delivered. 

The 10-week web-based program will be administered by the administrating organization, Better Health Company (BHC), and is delivered during the year at primary school terms and midterms. In Australia, there are four school terms per year. The midterm programs will start approximately 6 weeks into the school term. Participants will be recruited for a school term or midterm program; a new recruitment cycle will begin, at the latest, 2 weeks prior to the commencement of the next earliest term or midterm program. Participants recruited during a school term or midterm recruitment cycle will only be considered for a school term or midterm program, respectively. Following study enrolment, participants allocated to the intervention group (Cohort 1) will complete the program in the subsequent commencing school term or midterm, whereas participants allocated to the control group (Cohort 2) will complete the waitlist control period in the next commencing school term or midterm. Participants allocated to the control group will not receive any intervention during the 10 weeks control period and will receive the (same) web-based program in the school term or midterm following the waitlist control term. Study involvement for each participant will run from baseline to 12-months post-program completion. 

Families who consent to the study will be randomized into the intervention or waitlisted control group. The randomization schedule was generated using block randomization (1:1 ratio) from Research Randomizer [41]. Group allocation will not be communicated to the BHC. Instead, study investigators will allocate participants to the respective school term or midterm in BHC’s data management system. In doing so, BHC’s health coaches, who are assigned to and have direct contact with families during the program, will be blinded to the study allocation.

### 2.3. Study Population

#### 2.3.1. Eligibility

This study/program focuses on the family unit. Study participants will, therefore, involve the child(ren) who meet the following inclusion criteria and at least one parent/caregiver. The eligibility criteria accounts for the inclusion criteria of the web-based program and the characteristics of participants who would benefit most from a family-centered program and are developmentally mature enough to complete research activities. 

##### Inclusion Criteria

The inclusion criteria are children aged 7–13 years (inclusive) with overweight or obesity, as defined by the Centers for Disease Control and Prevention (i.e., BMI ≥ 85th percentile), and living in Victoria, Australia [42]. Children will be generally healthy, defined as an absence of clinical or comorbid conditions that require medical clearance to participate. Children with a learning or behavioral disability will be included if their condition does not impact their ability to engage in the program. Children will also have at least one parent/caregiver who will accompany and support them with study/program activities and can provide informed consent. Children will meet all inclusion criteria of the web-based program as it would typically run, including being able to attend weekly coaching appointments scheduled on weekdays at 15:00–21:00. There are no other inclusion criteria for parents/caregivers.

##### Exclusion Criteria

Children will be excluded if they are within their healthy weight range or underweight (i.e., BMI 5th–84th or <5th percentile, respectively). Children will also be excluded if they are engaging in other weight management programs (structured or referred) and will not be discontinuing the program during the study time period. Children who have participated in or completed other program(s) delivered by BHC in the past 12 months will be excluded. Other exclusion criteria include having a sibling who is completing or already completed the study, being unable to understand or communicate in English, or lacking access to a device to access online resources and complete study/program activities.

#### 2.3.2. Sample Size Estimation

The primary outcome will be the change in BMI z-score from baseline to 10 weeks. An a priori power analysis was conducted using G*Power version 3.1.9.4 [43] to estimate the sample size needed to detect a difference in the mean change in BMI z-score between the intervention and control group from baseline to 10 weeks using a *t*-test. The sample size estimation accounted for a possible reduction in BMI z-score within the control group, an effect size based on BHC’s pilot data, and a 30% attrition rate based on previous trials on a similar program (trials on the MEND program reported a 30% attrition) [44]. The effect size based on the change in BMI z-score and informed by pilot data was 0.6 (i.e., medium effect size using Cohen’s (1988) [45] criteria). With a 5% significance and 80% power, this study aims to recruit *n* = 118 participants (*n* = 59 intervention group; *n* = 59 control group) to observe a difference in the primary outcome measure between groups with this effect size using a *t*-test. 

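### The target of 118 children does not give 80% power at d = 0.6 once the protocol's own 30% attrition is taken off; the figure matches 45 × 1.3 rather than 45 / 0.7

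*Protocol article*

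**What the plan says.** Section 2.3.2 (Sample Size Estimation) sets out the calculation for the primary outcome, the between-group difference in mean change in BMI z-score from baseline to 10 weeks, compared by t-test. The elements are:

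- Software: "An a priori power analysis was conducted using G*Power version 3.1.9.4".
- Effect size: "The effect size based on the change in BMI z-score and informed by pilot data was 0.6".
- Attrition: the estimate is said to account for "a 30% attrition rate based on previous trials on a similar program".
- Error rates and target: "With a 5% significance and 80% power, this study aims to recruit" 118 participants, 59 in each group.

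Section 2.2 gives 1:1 block randomization, and section 2.7 confirms the independent t-test on change as the primary comparison. The article prints neither the number of analysable children required before the attrition allowance, nor the formula for that allowance, nor whether the 5% is one- or two-sided.

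**The concern.** An allowance for attrition should ensure that, after the expected loss, the number left is at least the number the power calculation requires. To do that, the required number is divided by the proportion retained. A common slip is to multiply by one plus the attrition rate. At 30% the two differ noticeably: 1 / 0.7 = 1.43 against 1.30. The printed target agrees with the second route and not the first.

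Section 2.3.2 is the only justification given for the trial's size. If the 80% does not hold at the assumed attrition, a non-significant primary result would be read against a power the trial was never expected to have.

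**Working it through.** **Inputs.** d = 0.6, 5% significance, 80% power, 30% attrition and an independent t-test come from section 2.3.2. The 1:1 allocation comes from section 2.2. A two-sided test is my assumption, since the article does not say.

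**Method.** Exact power of the two-sample t-test from the noncentral t distribution, with n per arm, 2n − 2 degrees of freedom and noncentrality d × √(n/2).

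**Step 1: analysable children required.**
- n = 44 per arm: power 79.5%.
- n = 45 per arm: power 80.4%.

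So 45 per arm are needed, 90 in total.

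**Step 2: reproduce the protocol's figure.**
- 45 × 1.3 = 58.5, rounded up to 59 per arm, 118 in total. This matches the article exactly.
- 45 / (1 − 0.30) = 64.3, rounded up to 65 per arm, 130 in total. This does not match.

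Other routes that use d = 0.6 also miss 59:

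| Variant | Analysable per arm | ÷ 0.7 | × 1.3 |
|---|---|---|---|
| Two-sided, 80% power, exact t | 45 | 65 | **59** |
| Two-sided, 80% power, normal approximation | 44 | 63 | 58 |
| One-sided, 80% power, exact t | 36 | 52 | 47 |
| Two-sided, 90% power, exact t | 60 | 86 | 78 |

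Nor can 59 be the number before attrition. With 59 analysed per arm, power would be 89.8%, not 80%.

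**Step 3: what 118 delivers at 30% attrition.**
- 59 × 0.7 = 41.3 per arm, so 82 to 83 children analysed.
- Power at d = 0.6 is 76.5% with 41 per arm and 77.0% with 41 and 42.
- Averaging over random dropout at 30% gives 76.6%.
- The effect detectable with 80% power at 41 per arm is d = 0.626.

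**Step 4: attrition that 118 can absorb.** 1 − 45/59 = 23.7%, that is, at most 14 losses per arm. At 30%, the expected loss is 59 × 0.3 = 17.7 per arm.

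**Size of the gap.** 130 − 118 = 12 children, or about 3 to 3.5 percentage points of power.

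**The case against.** Four points can be made for the protocol.

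1. **The multiplication is inferred.** The article prints no formula, and the effect size is given to one decimal from pilot data. If the value entered in G*Power was between about 0.627 and 0.634, the requirement is 41 per arm, and 41 / 0.7 = 58.6, which rounds up to 59. That would be correct inflation of an unrounded effect. It cannot be excluded, though the window is narrow and 45 × 1.3 uses the printed 0.6 as it stands. It also does not remove the problem. The article says the trial is sized for 0.6, and 0.6 does not lead to 118.

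2. **The test might be one-sided.** A one-sided 5% test would still have about 85% power at 41 per arm. Nothing in the article announces a one-sided test, however, and neither way of inflating the one-sided requirement gives 59.

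3. **The shortfall is small.** This is true. The 30% is borrowed from trials of a similar program and is uncertain in itself. Randomization, type I error and the validity of the primary comparison are untouched.

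4. **An article condenses the full protocol.** That would answer a complaint about missing detail. Here the effect size, significance level, power, attrition and target are all printed, and they are inconsistent with one another.

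What stands is that the mechanism should be described as likely rather than established, and that the consequence is modest.

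**Conclusion.** The concern holds. On the printed inputs, with 5% read as two-sided, 118 children less 30% attrition give 76.5% to 77% power for d = 0.6, not 80%. The number that supports the stated claim is 130. The target of 118 retains 80% power only if attrition stays at or below about 23.7%. That 59 arose as 45 × 1.3 is an inference from an exact match; the shortfall itself does not depend on how 59 was reached. The gap is 12 children and about 3 to 3.5 points of power. It does not threaten the trial's validity, but the stated power is wrong as written and should be corrected before results are read against it.

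**What to change.** Keep 118 and correct the statement in section 2.3.2, for example: 118 randomised; with 30% attrition about 82 analysed (41 per arm), giving 76% to 77% power for d = 0.6 with a two-sided 5% t-test; 80% power is kept if attrition is at most about 23%. The same sentence should give the required analysable number (45 per arm) and the inflation formula. If the pilot effect was rounded to 0.6, print the unrounded value. This costs one sentence and no extra participants.

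If the sponsor prefers to keep the claim of 80% power at d = 0.6 with 30% attrition, the target becomes 130, which is 12 more children.

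A baseline-adjusted ANCOVA in place of the t-test on change could recover part of the loss, but that is a separate design choice and the correction does not depend on it. It divides the standardised effect by √((1 + r)/2), where r is the baseline to 10-week correlation. At 41 per arm this gives about 81% power if r = 0.8 (effective d = 0.632) and about 79% if r = 0.9 (effective d = 0.616). Both correlations are assumptions; the article gives none.

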#### 2.3.3. Recruitment

BHC will recruit participants to complete the web-based program from their established networks in Victoria, including promoting the study among local government councils, schools, non-profit or private organizations, general practitioners, and other health professionals. BHC will advertise through flyers, posters, newsletters, social media posts (e.g., via Facebook, Instagram), and/or electronic correspondence. BHC will also use promotional strategies, including running family-focused media campaigns, keeping social media accounts up-to-date with recruitment information (e.g., promotional events, nearing the end of a recruitment phase), and reaching out to youth/parent-focused groups and/or health professionals in regional areas of Victoria.

Study investigators will also support recruitment by communicating with and disseminating promotional resources to professional networks.

Interested families can self-refer by completing an online registration form. Healthcare professionals may also refer participants by completing an online referral form. Once an online referral is received, a profile will be generated in BHC’s data system, including the participant’s unique identifier number. BHC will contact the families to outline the program and the relationship with the research, provide key information on the study, and conduct initial screening with participants for eligibility in the program and research. If families are willing to participate in this study, BHC will obtain verbal consent from the families for their contact details to be provided to study investigators. Study investigators will contact the families to address their queries or concerns if received and noted by BHC, confirm their eligibility for the research, and obtain written consent from the parent/caregiver and assent from the child(ren) prior to randomization.

### 2.4. Intervention

The BHPO is a 10-week web-based program designed for families that aims to promote healthy behavior changes. The program is a multi-component program, primarily delivered via a website where participants have access to weekly modules/activity sessions. There are 10 modules covering topics such as the five food groups, healthy eating behaviors/habits, reading food labels, the importance of and ways to increase movement, and healthy family routines. The participating child(ren) and at least one parent/caregiver will apply the information presented in each module by completing weekly online activities/exercises, available to families at the end of each module. Families participating in the program also receive weekly phone coaching calls with qualified health professionals such as dietitians, nutritionists, and exercise physiologists to set weekly targets on and develop action plans to achieve healthy behavior changes. Families also receive email/SMS communication to follow up with their progress throughout the program, access to a closed Facebook group with posts shared by other families who have previously participated or are currently participating in the program, and prize incentives upon completion. The program activities are designed to involve the family unit; the activities (e.g., learning and applying the information on healthy eating and physical activity, attending coaching sessions, making gradual behavior changes to meet weekly targets) are expected to be completed by the participating child(ren) and at least one parent/caregiver. The program is also designed and expected to allow the flexibility for household members other than the participating child and parent/caregiver to engage with the program contents (e.g., information, development and manifestation of action plans to meet targets/achieve healthy behavior changes). The program is delivered free of charge to participating families by BHC. The BHPO is adapted from the in-person, group-based version, which has been successfully delivered and evaluated in Australia for over a decade, and consistent with evidence-based guidelines on healthy eating, physical activity, and behavior changes [40].

No advice is provided to participants allocated to the control group during the waitlisted control period.

### 2.5. Data Management

Data collection and management follows the Monash Research Data Management Policy and data will be stored securely on Monash University supported servers and at the Monash University Be Active Sleep Eat (BASE) facility. All information collected by BHC at recruitment and during program administration will be stored in BHC’s online, password- and firewall-protected data system and will follow BHC’s privacy policy. All data and results will be deidentified and managed confidentially at all stages during the study.

Information on data collection and management is provided to participants (children and parents/caregivers) in the study explanatory statements (both parent/caregiver and child versions); these forms are emailed to parents/caregivers along with the study consent forms, and when study investigators are obtaining written consent from participants and prior to randomization.

### 2.6. Outcome Measures

Outcome measures will be self-reported via surveys administered online, at baseline, post-program completion (10 weeks), and 6- and 12-months post-program completion. Participants allocated to the control group will be asked to complete an additional set of surveys following the 10 week control period. All study assessments will be administered online via a Research Electronic Data Capture (REDCap) [46,47] link, Australian Eating Survey (AES) [48], or Youth Activity Profile (YAP) [49] link, and distributed to participants via email.

Qualitative data will also be collected online through video conferencing and real-time transcribing platforms (Zoom [50], Otter.ai [51]) at 3 months post-program completion.

All study assessments, including study surveys and interviews, will be completed by both the participating child and parent/caregiver. All outcome measures will be self-reported by participants to complement the virtual nature of the intervention and include the participation of families from all geographic locations of Victoria. A study by Chai and colleagues supports the use of parent-reported measurements that are collected online for web-based lifestyle programs [52]. The study found that Australian parents of primary-school-aged children were relatively accurate in reporting their child’s anthropometric measurements, including their weight and height [52]. 

The primary outcome measure is the change in the child’s BMI z-score. Secondary outcomes include (the change in) the child’s BMI z-score, waist circumference, dietary intake, physical activity, quality of life, and the participating child and parent/caregiver’s experience of completing the program. Details on the collection of the outcome measures are summarized in Table 1.

The web-based program also includes surveys to be completed by participants as a part of the program activities. Data collected from these surveys may supplement data collected by study investigators, to inform outcome measures. 

### 2.7. Data Analysis

All statistical analysis of quantitative data will be performed using IBM SPSS Statistics version 25 [46] and methods were confirmed with and reviewed by the Monash study statistician ([name]). 

The primary focus of this study is to test whether the web-based program has an effect on BMI z-score over a 10-week period. An independent *t*-test will be used to compare the difference in the mean change in BMI z-score between Cohort 1 and 2 from baseline to 10 weeks. Independent *t*-tests will also be used to compare the differences in the quantitative outcome measures between cohorts from baseline to 10 weeks. A 2 × 2 mixed ANOVA will be conducted to investigate the impact of the web-based program (between factor: web-based program vs. control) on BMI z-score from baseline to 10 weeks (within factor). Separately, mixed model ANOVAs will also investigate the impact of the web-based program on the secondary outcome measures (i.e., WC, diet quality score, physical activity score, and quality of life scores) from baseline to 10 weeks. The impact of being waitlisted (Cohort 2) will be explored to ascertain whether receiving the web-based program following 10 weeks of waiting will differ on the quantitative outcome measures from Cohort 1 over time. If being waitlisted does not have an impact on the quantitative outcome measures (as anticipated), a one-way repeated measures ANOVA will be used to assess the effect size of the web-based program on quantitative outcome measures overtime with greater certainty (i.e., power). Independent *t*-tests may also be used to compare the differences in the mean changes in quantitative outcome measures between cohorts or compare the mean differences in quantitative outcome measures for all participants at immediately pre-program (baseline or post-10-weeks waitlisted period) and post-program completion. 

As the goal of including a qualitative component in this study is to understand lived experience, reflexive thematic analysis will be used to explore participants’ experiences of the web-based program [54,55]. Evaluation studies on similar e-Health programs largely lack the use of qualitative approaches; therefore, an inductive vs. a deductive coding approach [54] will be used and performed using NVivo [56]. The process of reflexive thematic analysis will include the following stages [54,55,57]: study investigators will read the transcripts of the interview sessions generated from the Zoom videoconferencing platform [50] to familiarize with the data. Study investigators will develop codes and a coding framework from the transcripts to code the transcripts thereafter. Study investigators will develop themes from the codes and coded data. Themes will be reviewed and further developed with the codes and coded data. The themes will then be grouped into broader categories to make sense of the data. The qualitative findings will add to the statistical findings of this study.

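### The primary test is an unadjusted t-test on change although baseline BMI z-score is collected; it is valid, but baseline-adjusted ANCOVA is more efficient unless baseline and 10-week values correlate almost perfectly

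*Protocol article*

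**What the plan says.** Section 2.3.2 defines the endpoint: "The primary outcome will be the change in BMI z-score from baseline to 10 weeks". The sample size is built for a t-test on that change. Section 2.7 gives the matching analysis, an independent t-test that "will be used to compare the difference in the mean change in BMI z-score between Cohort 1 and 2 from baseline to 10 weeks".

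The same paragraph applies independent t-tests to the other quantitative outcomes over the same interval. It then adds a second analysis of the primary outcome: a 2 × 2 "mixed ANOVA will be conducted to investigate the impact of the web-based program (between factor: web-based program vs. control) on BMI z-score", with time (baseline, 10 weeks) as the within factor. Similar mixed ANOVAs are planned for waist circumference, diet quality, physical activity and quality of life.

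None of these analyses names the baseline value, or anything else, as a covariate. The baseline values will be available; Section 2.6 says: "Outcome measures will be self-reported via surveys administered online, at baseline, post-program completion (10 weeks), and 6- and 12-months post-program completion". The control group completes an additional survey after its 10-week waiting period.

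**The concern.** A change score gives the baseline a fixed coefficient of 1. When the baseline to 10-week correlation is below 1 and the spread is similar at both visits, the best coefficient is rho, not 1, and change is negatively correlated with baseline. A t-test on change ignores that relation and pays in two ways:

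- The treatment contrast has a larger variance than it needs.
- If the arms differ at baseline by chance, the change score over-corrects, and an error proportional to (1 − rho) stays in the estimate.

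The 2 × 2 ANOVA does not help. With two groups and two times, its interaction is the t-test on change in another form. Section 2.7 therefore plans the same unadjusted comparison twice and the adjusted one not at all. At stake is precision on the primary contrast and on each secondary contrast of a small trial.

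**Working it through.** **Inputs from the document (Section 2.3.2, except allocation from Section 2.2).** 5% significance and 80% power; standardised effect d = 0.6 on the change in BMI z-score; 1:1 allocation; 30% attrition; 59 per arm, 118 in total.

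**Assumptions.** Two-sided test (sidedness is not stated); equal SDs at baseline and 10 weeks; rho from 0.5 to 0.99. The document gives neither rho nor any SD.

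**1. The plan's own figure.** A two-sided two-sample t-test with d = 0.6 and 80% power needs 44.6, so 45 per arm. Then 45 × 1.3 = 58.5, so 59 per arm and 118 in total. The planned number is reproduced.

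**2. Completers.** 59 × 0.7 = 41.3, so 41 per arm. The t-test then has noncentrality 0.6 × √(41/2) = 2.717 on 80 df, which gives power **76.5%**.

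**3. Variance of ANCOVA relative to the change score.** With unit variance at each visit, the change score has variance 2(1 − rho) and the ANCOVA residual has variance 1 − rho². The ratio is (1 − rho²) / [2(1 − rho)] = (1 + rho)/2. The effective standardised effect is therefore 0.6 / √[(1 + rho)/2].

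**4. ANCOVA power at 41 per arm.** One df is deducted (79 left), and the noncentrality is multiplied by √(1 − 1/79) for the estimated slope.

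| rho | variance ratio | effective d | power | gain over 76.5% (points) |
|---|---|---|---|---|
| 0.5 | 0.750 | 0.693 | 86.8% | +10.3 |
| 0.7 | 0.850 | 0.651 | 82.4% | +5.9 |
| 0.8 | 0.900 | 0.632 | 80.3% | +3.8 |
| 0.9 | 0.950 | 0.616 | 78.1% | +1.6 |
| 0.95 | 0.975 | 0.608 | 77.0% | +0.5 |
| 0.97 | 0.985 | 0.605 | 76.6% | +0.1 |
| 0.99 | 0.995 | 0.602 | 76.2% | −0.3 |

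Simulation with 40,000 trials per setting agreed: at 41 per arm, ANCOVA rejected in 86.8%, 80.2%, 78.1% and 77.0% of trials at rho 0.5, 0.8, 0.9 and 0.95. Under no effect (rho 0.5, 0.9 and 0.95), both methods rejected in about 5%.

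**5. Chance imbalance.** In simulated trials whose baseline means differed by more than 0.3 SD, the change-score estimate was off on average by about 0.20 SD at rho 0.5, 0.04 SD at 0.9 and 0.02 SD at 0.95. ANCOVA was off by about 0.005 SD or less.

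**6. Duplicate test.** In one simulated data set (41 per arm), the t-test on change gave t² = 4.391 and the group-by-time interaction gave F = 4.391, both with p = 0.0393 on 80 df.

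**The case against.** The plan is internally consistent: the endpoint is change, the sample size is for a t-test on change, and the analysis is that t-test. Under randomisation the test is unbiased and keeps its type I error. All of that stands, so this is a loss of efficiency and not an error.

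The gain also depends on a correlation that the document does not give. BMI z-score measured again after 10 weeks may track closely, and then ANCOVA adds little; near rho 0.98 and above, the lost degree of freedom slightly outweighs the gain. Against that, height and weight are family-reported and may be measured at home, and entry is restricted to the 85th percentile or above. Both could lower rho, but by how much is unknown. This part of the objection limits the size of the point and does not remove it.

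Three stronger readings are tempting, and the document does not support them.

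- **That baseline imbalance goes wholly uncorrected.** Subtracting baseline already removes most of it when rho is high, as step 5 shows.
- **That the group main effect of the ANOVA will be taken as the program effect.** That effect averages baseline with 10 weeks and so halves the contrast; at 41 per arm its power would be only about 9% (rho 0.9) to 15% (rho 0.8). But Section 2.7 is labelling the two factors of the design. It does not say which term is the test, and the primary t-test stands separately.
- **That running the same test twice inflates error.** The two p-values are identical, so the duplication is harmless redundancy.

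Finally, the figure of 41 completers reflects how attrition was allowed for (45 × 1.3 instead of 45/0.7, which gives 65 per arm). That is a separate matter and should not add weight here.

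**Conclusion.** The point holds as a recommended improvement. The primary analysis fixed in Section 2.7 is valid but less efficient than it could be with data the trial already collects. At 41 per arm and d = 0.6, ANCOVA changes power from 76.5% to between 86.8% (rho 0.5) and 76.2% (rho 0.99). The gain is material up to a rho of about 0.8, under 2 points at 0.9 and nil at about 0.97. The largest loss in the range examined is about 0.3 points.

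These figures assume a two-sided test, equal SDs at the two visits and 30% attrition. They apply to BMI z-score only: the document says "The effect size based on the change in BMI z-score and informed by pilot data was 0.6" and gives no effect size for the secondary outcomes. For those, only the variance ratio (1 + rho)/2 carries over; a questionnaire score with a lower rho would gain more.

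A reader might infer that ANCOVA restores the planned 80% power. It does so with 41 completers per arm only if rho is about 0.8 or lower.

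**What to change.** In Section 2.7:

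- Make the primary analysis an ANCOVA of 10-week BMI z-score on randomised arm with baseline BMI z-score as covariate. Report the adjusted mean difference with its 95% confidence interval.
- Use the same model for waist circumference, diet quality, physical activity and quality-of-life scores, each adjusted for its own baseline.
- Keep the t-test on change as a sensitivity analysis.
- Drop the 2 × 2 mixed ANOVA, or state that its group-by-time interaction is the effect of interest.

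The cost is a change of wording and one degree of freedom. No new data are needed. This does not replace a check of the attrition allowance in the sample size.
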